## Abstract

**Background:**

Staging laparoscopy(SL) is a recommended technique for the staging of Gastric Cancer(GC) and provides the indication for a radical surgery. Considering the medical practice in China, the standardized and regular usage of SL is yet to be spread. However, existing guidelines vary and make an ambiguity of indication for SL. Besides, the specific indication for Chinese patients remains a niche. This study aims to the essential, missing information of Chinese patients and tries to normalize the indication of LS in medical practice in China.

**Methods:**

The study is a prospective, multicenter cohort study being conducted in China with a total of 450 patients, all diagnosed with locally advanced gastric cancer (cT2-4 N0-3 M0, no evidence of intra-abdominal dissemination) through Computed Tomography(CT) and/or Endoscopic Ultrasonography(EUS). Peritoneal lavage is regularly performed during the SL. Multivariate Cox regression model and receiver-operator characteristic(ROC) analysis will be used to analyze the significant risk factors of intra-abdominal metastasis(including peritoneal dissemination and a positive cytological result).

**Discussion:**

This confirmatory study will provide us with the specific positive rate of intraabdominal metastasis of GC in China, compared with empirical evidence of 20%. We expect this trial will contribute to our discovery of the specific risk factors of intra-abdominal metastasis of Chinese patients and to the stimulating and performing of minimally invasive surgical procedures.

**Trial registration:**

ClinicalTrials.gov: registration number NCT02172690.

## Background

Gastric cancer is a major cause of cancer death worldwide with a 40 percentage of cases occurring in China [1]. Individualized treatment based upon tumor stage takes on a widely accepted strategy, and surgery remains the most effective treatment modality.

Most of the Chinese patients are diagnosed with locally advanced stage, suffering the substantial intra-abdominal metastases with higher risks. Precise preoperative staging is particularly important for therapeutic strategies and prognostic evaluation.

Precise staging is a foremost method that benefits the successful surgical intervention of cancer, contributed to the improvement of medical tools: despite the fact that preoperative imaging techniques have significantly improved the diagnostic accuracy of wall infiltration and lymph node involvement, the detection of peritoneal dissemination still needs to be developed; positive intra-peritoneal findings of free cancer cells has been proved to be related with poor survival yet could only be confirmed during surgical procedure [2, 3].

SL has been suggested useful in detecting unrecognized peritoneal dissemination, and in collecting peritoneal lavage fluid for cytological examination with minimal invasion. However, indication for SL remains controversial. NCCN guideline recommends an indication for SL of T3 and/or N+; ESMO, IB-III; JGCA, none, merely mentioned SL only on the condition of neoadjuvant Chemoradiotherapy [4–6]. No specific recommended indications for Chinese patients can be referred to for lack of solid evidence.

The aim of this study is to acquire a basic data on the positive rate of SL in Chinese patients and to identify the risk factors associated with intra-abdominal metastasis.

## Methods

### The design of study

This study evaluates the efficacy of SL with peritoneal cytology, and determine the indications if possible.

Patients who meet the inclusion criteria will be enrolled consecutively, with their preliminary data collected using a web-based case report form. When the whole data-collecting is completed, factors associated with intra-abdominal metastasis will be analyzed by multivariate Cox regression model. Receiver-operator characteristic (ROC) will be used to find out risk factors of intra-abdominal metastasis. Figure 1 shows the CONSORT diagram.

**Fig. 1 Fig1:**
[figure not shown]
CONSORT diagram of study

#### Recruitment

Patients with pathologically confirmed gastric adenocarcinoma are recruited. If the patient meets all inclusion criteria, following data will be recorded: basic information including age, gender, height, body weight et al., clinical information including CT stage(enhanced CT is mandatory required), EUS stage, result of blood examinations such as tumor marker (CEA, CA19-9, CA72-4, CA12-5), blood cell count, albumin et al. If there been any differences between CT & EUS, it is required to record them separately.

#### Staging laparoscopy

If the patient is confirmed at stage cT2-4bN0-3 M0, which means no sign of distant metastasis detected by CT/EUS, he/she undergoes SL. Following data will be recorded: intraoperative finding including the peritoneal dissemination, and the peritoneal lavage; video of surgery and pictures demonstrating the extent of peritoneal dissemination is required.

#### Follow-up

Postoperative hospital stay and complications will be recorded, the follow-up time will be 30 days after surgery. Only those who undergoes DL alone will be included into safety analysis since the complications will be confused if the patient undergo radical surgery immediately after SL.

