#### Study endpoint

The primary target of this study is to obtain the result of SL. Either peritoneal dissemination or a positive result of cytological examination will be recorded as a positive result. If the pathological or cytological examination describes “suspicious”, the result will be characterized as positive, consistent with our current practice.

The secondary aim is to evaluate the safety of SL.

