### Selection of candidate patients

Age ≥ 18;Histological confirmed diagnosis of primary gastric carcinoma (including esophagus-gastric junction).Karnofsky score ≥ 70;Abdominally enhanced spinal CT and endoscopic ultrasonography (EUS) showed a clinical stage of T2-4bN0-3bM0;Fit for radical gastrectomy or neo-adjuvant chemotherapy;Willing to comply with protocol, and provide informed consent forum.

The exclusion criteria included:Unfit for laparoscopic operation or general anesthesia (suspicious abdominal adhesions, severe cardiopulmonary disease, etc.);Underwent emergency surgery to relieve obstruction, bleeding or perforation.

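### The safety analysis is limited to patients who have laparoscopy alone, so it leaves out complications of SL recognised before resection in patients who go straight on to radical surgery

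*Protocol article*

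**What the plan says.** The Study endpoint section states the safety objective without restriction: "The secondary aim is to evaluate the safety of SL".

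The Follow-up section describes the safety data: "Postoperative hospital stay and complications will be recorded", and "the follow-up time will be 30 days after surgery". It then limits the analysis set: "Only those who undergoes DL alone will be included into safety analysis since the complications will be confused". The confusion it has in mind arises when resection follows directly, or in its words "if the patient undergo radical surgery immediately after SL". DL is not in the article's list of abbreviations; I read it as the same procedure as SL.

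Three other places bear on who ends up in that set or on what is collected.

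- The Abstract (Background) says that SL "provides the indication for a radical surgery".
- The eligibility list admits patients who are "Fit for radical gastrectomy or neo-adjuvant chemotherapy".
- The Staging laparoscopy section lists the operative data as "intraoperative finding including the peritoneal dissemination, and the peritoneal lavage", and asks for video of the surgery. It does not name intraoperative complications.

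The article gives no separate analysis of intraoperative SL events in patients who proceed to resection, and no rule for who has laparoscopy alone.

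**The concern.** The aim and the analysis set do not match. The aim is the safety of SL; the set is those SL patients who have no radical operation straight afterwards. Two problems follow.

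First, the reason given is narrower than the rule. Attribution is a real difficulty for length of stay and for a complication that appears after a combined operation. A trocar injury or a bleed recognised during SL, before resection has begun, does not share that difficulty. The rule makes no distinction and excludes both.

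Second, membership of the set is decided after the procedure whose safety is being measured. The operative finding is at least one influence on whether resection follows, and an SL complication could be another. For illustration only: a patient whose planned resection is called off after an SL injury would enter the set, while a patient with a repaired injury who proceeds to resection would leave it. Selection of this kind can move the estimated rate either way.

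At stake is the secondary objective. A study meant to help define who should have SL would report a complication rate for a selected part of the patients who have it. The primary positive rate is not affected.

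**Working it through.** **The plan's own figure.** The only calculated number is the sample size, used here as the denominator. Inputs from the Sample size section: reference rate 15%, expected rate 20%, two-sided 5%, power 80%, dropout 5%.

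n = [(1.960 × √(0.15 × 0.85) + 0.842 × √(0.20 × 0.80)) / 0.05]² = 429.7, so 430.

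430 / 0.95 = 452.6, so 453. This agrees with the stated 450 to within 1%. The safety point does not depend on this derivation.

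**What the stated reason covers.**

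| Type of event | Is attribution blurred by immediate resection? | Analysed in patients who go straight to resection? |
|---|---|---|
| Hospital stay | Yes | No |
| Postoperative complication within 30 days | Yes | No |
| Access injury or bleeding during SL, recognised before resection starts | No | No |
| Anaesthetic event, or SL injury recognised late | Often | No |

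The rule goes further than its reason in the third row only.

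**What determines the set.** The Abstract ties radical surgery to the SL finding, so the finding is one determinant. The eligibility list also allows a neo-adjuvant route, by which an SL-negative patient could have laparoscopy alone. The set is therefore fixed after SL and depends partly on its result. The article does not let its size be computed.

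**Precision under assumed sizes.** The shares are assumptions. The comparison is for one outcome, an intraoperative SL event, counted either in the laparoscopy-alone set or in everyone.

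- One-sided 95% upper limit with zero events in m patients: 1 − 0.05^(1/m).
- Chance of at least one event at an assumed true risk of 1%: 1 − 0.99^m.

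| Share of 450 | Analysed (m) | Left out | Upper limit, zero events | Chance of at least one event |
|---|---|---|---|---|
| 20% | 90 | 360 | 3.3% | 60% |
| 50% | 225 | 225 | 1.3% | 90% |
| 70% | 315 | 135 | 0.9% | 96% |
| 100% | 450 | 0 | 0.66% | 99% |

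The 20% row would apply if exactly the expected SL-positive share had laparoscopy alone. Taking 428 patients after 5% dropout (450 × 0.95 = 427.5) changes little: the upper limits become 3.4%, 1.4%, 1.0% and 0.70%.

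**The case against.** The strongest defence is that the restriction is stated openly, comes with a reason, and suits the data described, which are mainly postoperative and run to 30 days. For those outcomes an SL effect cannot be separated from that of an immediate gastrectomy, and the fix below keeps the same set for them. This part stands.

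It can also be said that this is a condensed article and that adverse-event definitions belong in the full protocol. That would answer a complaint about missing detail. It does not answer this point, because the article states the analysis set, applies it to the whole safety analysis, and makes no exception for intraoperative events.

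A reader might infer more than the text supports in three ways.

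- **That the SL result alone picks the set, with positive patients never having radical surgery.** The article does not say so. The neo-adjuvant route allows laparoscopy alone after a negative SL. No turnaround time is given for cytology, so a resection before a positive result is known is not ruled out.
- **That the excluded events are lost.** The Follow-up section does not confine recording to laparoscopy-alone patients. Only the analysis is restricted.
- **That every intraoperative event can be assigned to SL.** SL is done under general anaesthesia, which a patient going straight to resection would need in any case. An injury may also come to light only during or after resection.

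Finally, safety is a secondary aim with no stated hypothesis or threshold. That limits the weight of the point but does not remove the mismatch.

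**Conclusion.** The point holds in a limited form. The safety rule is broader than its reason: it leaves SL-specific intraoperative events recognised before resection out of the analysis for every patient who proceeds directly to radical surgery. What remains is a set formed after the procedure and partly by its findings. Its complication rate cannot be presented as the safety of SL in all patients who have it.

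The consequence for precision depends on a share that the article does not give. It ranges from large (upper limit 3.3% against 0.66% if 20% have laparoscopy alone) to modest (0.9% against 0.66% if 70% do). The documents do not show that the set will be small. These limits also say nothing about the size or direction of a selection bias, which cannot be estimated from the article. The selection problem remains at any share below 100%.

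This is worth correcting because the correction is cheap. It does not threaten the primary result.

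**What to change.** Replace the single safety set with two.

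1. **All patients in whom SL is started:** SL-specific intraoperative complications, such as access injury or bleeding, recognised up to the end of SL or the start of resection, whichever comes first.
2. **Patients who have laparoscopy alone:** 30-day complications and postoperative stay, reported by SL result and labelled as a selected subset. Do not present this as the overall safety of SL.

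The cost is one added table, a change of wording and, if it is not already collected, one case report form item on when a complication was recognised. A short timing rule is needed for events at the transition from SL to resection. The surgical video may help with visible events but would not capture anaesthetic ones. Anaesthetic events and those recognised late remain hard to attribute in patients who go straight to resection, and the report should say so. The sample size, the primary analysis and patient management stay as they are.

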#### Study endpoint

The primary target of this study is to obtain the result of SL. Either peritoneal dissemination or a positive result of cytological examination will be recorded as a positive result. If the pathological or cytological examination describes “suspicious”, the result will be characterized as positive, consistent with our current practice.

The secondary aim is to evaluate the safety of SL.

### Selection of candidate patients

Age ≥ 18;Histological confirmed diagnosis of primary gastric carcinoma (including esophagus-gastric junction).Karnofsky score ≥ 70;Abdominally enhanced spinal CT and endoscopic ultrasonography (EUS) showed a clinical stage of T2-4bN0-3bM0;Fit for radical gastrectomy or neo-adjuvant chemotherapy;Willing to comply with protocol, and provide informed consent forum.

The exclusion criteria included:Unfit for laparoscopic operation or general anesthesia (suspicious abdominal adhesions, severe cardiopulmonary disease, etc.);Underwent emergency surgery to relieve obstruction, bleeding or perforation.

### SL technique

SL was performed under general anesthesia. The patient is placed in a supine position. A 10-mm disposable trocar (observing hole) is inserted into the sub-umbilicus, and a 30° telescope is used. Another 10-mm trocar and a 5-mm trocar (operating hole) are inserted into the right upper quadrant and left upper quadrant, respectively. Prior to any manipulation, 250 ml of warm normal saline is infused into subphrenic space, subhepatic space, omentum, bilateral paracolic sulci and the pouch of Douglas. The irrigation should be carefully operated to avoid the primary tumor. At least 100 ml of fluid is aspirated from the subphrenic space, subhepatic space and Douglas’ pouch. The fluid is immediately sent for centrifugation and cytological examination and a systematic inspection of the abdominal cavity is performed clockwise from the right quadrant. Any suspicious lesion will be biopsied and sent for frozen pathologic examination.

### Sample size

This study is a single arm OPC (objective performance criteria) design where the primary evaluation index is the positive rate of SL. Based upon literature, expected event rate is 20%, and clinical acceptable rate is above 15%. Type I error as bilateral 5%, dropout rate as 5%, power as 80%, calculated sample size is 450. The recruitment process is estimated to be completed by December 2016.

### Data analysis

Clinical characteristics of the DL- and DL+ patients are compared using the Independent samples group t test and chi-square test. To determine the risk factors, all variables found to be significant by the univariate analysis are assessed by binary logistic regression analysis (Method: Backward: Wald, probability for stepwise: 0.5 for entry, 1.0 for removal). The ROC curve and AUC analyses are used to determine sensitivity, specificity, and corresponding cut-off value of each factor. All *P* values < .05 are considered statistically significant. All statistical analyses are carried out using the SPSS statistical software package (version 20).

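### The ROC step stops at single-factor cut-offs read from the study cohort itself; carrying the planned logistic model into it would serve the indication aim better at little cost

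*Protocol article*

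**What the plan says.** All references are to the protocol article.

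- **Data analysis**, on risk factors: "all variables found to be significant by the univariate analysis are assessed by binary logistic regression analysis", with backward Wald selection.
- **Data analysis**, on ROC: "The ROC curve and AUC analyses are used to determine sensitivity, specificity, and corresponding cut-off value of each factor". No rule for choosing the cut-off is named, and no ROC of the fitted model or of a combined score is mentioned.
- **The design of study** gives ROC a different task: "Receiver-operator characteristic (ROC) will be used to find out risk factors of intra-abdominal metastasis". The same section says the study "evaluates the efficacy of SL with peritoneal cytology, and determine the indications if possible".
- **Abstract, Methods** describes one data source, a "prospective, multicenter cohort study being conducted in China with a total of 450 patients".
- **Sample size** is set for the SL positive rate, expected at 20% against a reference of 15%: "Type I error as bilateral 5%, dropout rate as 5%, power as 80%, calculated sample size is 450". No figure is attached to the ROC work.

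**The concern.** An indication has to say which patient should be offered SL, given several characteristics at once. A list of cut-offs, one per factor, does not say what to do with a patient who is above one and below another, and it gives no sensitivity for any combination. The logistic model would give each patient a single predicted probability, but the ROC step as written does not use it.

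There is also a same-sample problem. If a cut-off is picked because it separates these patients best, its sensitivity and specificity in these patients will on average be better than in new ones. Sensitivity matters most here, because its complement is the share of occult metastasis below the cut-off.

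Finally, two sections give the task of finding risk factors to different methods. A single-factor ROC curve adjusts for nothing else, so it cannot identify independent risk factors.

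**Working it through.** **1. The plan's own figure.** Inputs from Sample size: p0 = 0.15, p1 = 0.20, two-sided 5%, power 80%, dropout 5%. Normal approximation for one proportion:

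n = [1.960·√(0.15·0.85) + 0.842·√(0.20·0.80)]² / (0.20 − 0.15)² = [0.700 + 0.337]² / 0.0025 ≈ 430.

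Allowing for dropout, 430/0.95 = 453 (or 430 × 1.05 = 452), which agrees closely with the stated 450. The points below do not change this number.

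**2. Patients available to the ROC step.** 450 × 0.95 ≈ 428 evaluable. At 20% positive, this is about 86 positive and 342 negative.

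**3. Same-sample optimism.** The article gives no marker distribution, AUC or cut-off rule. Assumed: one normally distributed marker with equal variances, true AUC from 0.5 to 0.8, and the cut-off that maximises the Youden index J = sensitivity + specificity − 1. In each of 4,000 simulated cohorts of 428, apparent accuracy at the chosen cut-off was compared with true accuracy at that same cut-off. Optimism was taken before rounding.

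| True AUC | J apparent / true | Optimism in J | Sensitivity apparent / true | Specificity apparent / true |
|---|---|---|---|---|
| 0.50 | 0.073 / 0.000 | 0.073 | 0.558 / 0.498 | 0.515 / 0.502 |
| 0.60 | 0.193 / 0.130 | 0.062 | 0.607 / 0.556 | 0.585 / 0.574 |
| 0.70 | 0.331 / 0.277 | 0.054 | 0.675 / 0.631 | 0.656 / 0.646 |
| 0.80 | 0.482 / 0.438 | 0.044 | 0.749 / 0.712 | 0.733 / 0.726 |

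A separate simulation with exactly 86 positives and 342 negatives gave optimism of 0.072, 0.064, 0.053 and 0.044 at the same four AUC values.

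**4. What is not inflated.** The mean single-marker AUC was 0.600 for a true 0.60 and 0.701 for a true 0.70. Keeping only markers significant in the univariate test raised the 0.60 case to 0.610. A useless marker that passed that screen showed 0.582, but this happened in only 2% of runs (counting significance in the harmful direction). A binary factor has no cut-off to search for.

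**5. Stability of the cut-off.** Across cohorts the chosen cut-off had a standard deviation of 0.44 marker SD at AUC 0.60, 0.30 at 0.70 and 0.23 at 0.80.

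**6. Why single-factor figures do not fix a combined rule.** Take two factors, each with the true values at AUC 0.70 (sensitivity 0.631, specificity 0.646). The bounds below use those values alone.

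- Positive if either is positive: sensitivity lies between 0.631 and min(1, 0.631 + 0.631) = 1. Specificity lies between 0.646 + 0.646 − 1 = 0.292 and 0.646.
- Positive only if both are positive: sensitivity lies between 0.631 + 0.631 − 1 = 0.262 and 0.631.

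The accuracy of any joint rule depends on how the factors occur together, which factor-by-factor ROC does not report.

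**The case against.** **This is a condensed article.** Optimism correction, confidence intervals and the cut-off criterion may sit in a full protocol or analysis plan that is not shown. That stands, and their absence is not held against the plan. The point rests on what is written: ROC is applied to each factor, and two sections disagree about what it is for.

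**No cut-off rule is stated.** If cut-offs were fixed in advance, or chosen other than by maximising accuracy, the optimism would differ or vanish. Several recorded variables (sex, CT and EUS stage) are binary or have few levels and need little or no search. This stands, so the figures above are conditional.

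**The bias is modest.** A 5-point excess in sensitivity is about one standard error: √(0.6 × 0.4/86) ≈ 0.053. True, although an average bias is not removed by quoting a wide interval around the biased value.

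**Simple criteria are an accepted form of indication.** The Background reports guideline indications as stage criteria, which can be joined by and/or. The article does not say that the ROC cut-offs will themselves be the indication, and that aim is conditional. This limits the claim: one cannot say the study will issue a faulty rule. The accuracy of a joined rule would still have to be estimated jointly.

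**Stronger readings a reader might infer.**
- That the cut-offs and AUCs are themselves biased upward. The check does not show this: cut-offs are unstable, and single-factor AUC is essentially unbiased.
- That instability measures optimism. In a simulation of 3,000 cohorts with 85 positives and 342 negatives, the true sensitivity at the chosen cut-off ranged from 24% to 86% at AUC 0.60. That is scatter for a weak marker, and specificity moves the other way. Optimism correction would not remove it.
- That the main result is compromised. The primary measure is the SL positive rate, which uses no ROC analysis.

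**Conclusion.** The point holds in limited form. As written, the ROC step works on separate factors in the single study cohort and leaves the multivariable model unused, which suits the indication aim poorly. If continuous factors are cut at the maximum Youden index, the optimism in sensitivity plus specificity is about 0.04 to 0.07, mostly on sensitivity, and is smallest for the most useful markers. This rests on an assumed normal marker, the assumed cut-off rule, and about 86 positives and 342 negatives. The differing statements of what ROC is for are a plain inconsistency and need no assumption. I class this as a cheap improvement: it bears on a subsidiary analysis and leaves the primary positive rate and the 450 patients as they are.

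**What to change.** 1. In Data analysis, add an ROC analysis of the predicted probability from the final logistic model, and name it as the analysis that informs any indication.
2. Report AUC, sensitivity and specificity with bootstrap optimism correction and 95% confidence intervals. Repeat the univariate screen, backward selection and cut-off choice in every resample. This requires the cut-off criterion to be written down beforehand.
3. Keep the single-factor ROC curves, labelled as descriptive.
4. Reconcile the design section with Data analysis, so that identifying risk factors is assigned to the logistic regression and ROC describes discrimination.

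Cost: some extra programming on data already being collected, and accuracy figures that will look slightly less favourable. No additional patients or measurements are needed.
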